## Abstract

**Background:**

Anxiety is associated with poorer prognosis in patients with coronary artery disease (CAD). Due to their severity and chronic course, anxiety disorders, particularly generalized anxiety disorder (GAD) and panic disorder (PD), are of considerable interest and clinical importance in this population. This study has two main objectives: (1) to estimate the prevalence and incidence of GAD and PD in patients with CAD over a 2-year period and (2) to prospectively assess the association between PD or GAD and adverse cardiac events, treatment adherence, CAD-related health behaviors, quality of life and psychological distress.

**Design/Method:**

This is a longitudinal cohort study in which 3610 participants will be recruited following a CAD-related revascularization procedure. They will complete an interview and questionnaires at 5 time points over a 2-year period (baseline and follow-ups after 3, 6, 12 and 24 months). The presence of PD or GAD, adherence to recommended treatments, health behaviors, quality of life and psychological distress will be assessed at each time point. Data regarding mortality and adverse cardiac events will be collected with a combination of interviews and review of medical files.

**Discussion:**

This study will provide essential information on the prevalence and incidence of anxiety disorders in patients with CAD and on the consequences of these comorbidities. Such data is necessary in order to develop clear clinical recommendations for the management of PD and GAD in patients with CAD. This will help improve the prognosis of patients suffering from both conditions.

## Background

In Canada and in the United States, over 6% of adults aged 20 years or older live with coronary artery disease (CAD), the most common form of cardiovascular disease [1, 2]. Along with its elevated prevalence, CAD is also one of the costliest diseases in both countries, with annual direct and indirect costs reaching 219$ billions a year in the United States [2–4]. Although the incidence and mortality rates associated with CAD have decreased in the last decades, it remains one of the leading causes of mortality, hospitalization and disability-adjusted life years lost worldwide [1, 5, 6].

A variety of interventions may be used to manage the potential consequences of CAD and improve the prognosis of patients [7–9]. Given that up to 90% of the myocardial infarction risk is attributable to nine modifiable risk factors (e.g., cholesterol levels, hypertension, diabetes, smoking, obesity, physical inactivity, alcohol use, diet and psychosocial factors), comprehensive risk factor management programs and cardiac rehabilitation are essential to improve outcomes in patients with CAD [8, 10, 11]. The management of psychosocial risk factors represents a particular challenge: while decades of research have demonstrated their importance in patients with CAD, the nature and implications of the relationship between CAD and anxiety disorders is not as well understood as that of other CAD risk factors [12–17]. Although much of the research to date has focused on the role of depression, a growing number of studies suggest that anxiety may also lead to negative outcomes in this population [18–22].

### Anxiety and coronary artery disease

Elevated anxiety has been independently associated with a 36–88% increase in the risk of adverse cardiac events in patients with CAD [22–32]. However, the relationship between anxiety, CAD and CAD-related mortality remains unclear [33]. This may be partly due to the fact that anxiety, particularly anxiety disorders, remains understudied in the context of CAD [33]. One important issue is that most of the studies on this topic assessed anxiety with self-reported questionnaires [33]. This approach alone cannot be used to diagnose anxiety disorders which, due to their severity and chronic course, are more likely to have a significant impact on CAD prognosis [21, 28].

Two anxiety disorders, generalized anxiety disorder (GAD) and panic disorder (PD), are of particular interest and importance in patients with CAD as their prevalence rates among this clinical population (24 and 53% respectively), are up to 15 times higher than those in the general population [21, 33–39]. In patients with CAD, the presence of these disorders is also associated with an increased risk of major cardiac events, greater disability, higher psychological distress and lowered quality of life [21, 39–44]. Both disorders are also characterized by an increased suicidal risk and multiple and often unproductive medical consultations [45–50] as well as incident CAD and cardiac events [22, 51, 52]. Without treatment, PD and GAD have a chronic course and worsen over time, which negatively influence their prognosis and treatment response [46, 53–55].

Diagnosing anxiety disorders such as GAD and PD in patients with CAD can be challenging as there is a significant overlap in the somatic symptoms of both conditions (e.g. chest pain, dizziness, dyspnea, palpitations and tiredness) [20, 21, 33, 35, 56]. This may explain why anxiety disorders have been found to be more prevalent in the few studies in which they were diagnosed using structured interviews (the gold standard for psychiatric diagnoses) conducted by trained mental health professionals [33]. Furthermore, a single assessment point, as was used in several reviewed studies, might not be reliable in order to adequately identify pathological anxiety in patients with CAD [20–22, 24, 25, 27, 31–33]. Indeed, some authors have expressed concerns that assessing anxiety disorders shortly after a cardiac or life-threatening event may lead to false positives [28, 35]. In addition, the onset of a chronic illness such as CAD and dealing with its consequences are risk factors for the development of GAD and PD [57] and could lead to an elevated incidence of these disorders in the following months and years. Thus, further prospective studies using validated structured interviews and a robust methodology to assess the prevalence and incidence of PD and GAD in patients with CAD are needed [33].

### Possible mechanisms linking panic disorder and generalized anxiety disorder with CAD prognosis

Though still unclear, physiological and behavioral pathways have been proposed to explain how anxiety disorders and CAD influence each other and subsequently lead to poorer outcomes. Part of the association between CAD and anxiety disorders may be explained by physiological factors, such as increased inflammation [20, 21, 36, 39, 58]. Anxiety disorders are also associated with higher rates of hypertension, obesity, diabetes and dyslipidemia, which all increase the cardiovascular risk [21, 29, 59]. PD and GAD have also been linked to poorer health behaviors [20, 21, 36, 60–64]. For instance, the likelihood of alcohol use disorder, either dependence or abuse, is 79–83% higher in patients with GAD or PD than in patients without these disorders [65, 66]. These anxiety disorders are also associated with a 50–90% increased risk of daily smoking and nicotine dependence as well as low levels of physical activity [61, 63, 64, 67–70]. Furthermore, high levels of anxiety have been associated with non-attendance and non-completion of cardiac rehabilitation programs and non-adherence to cardiac medication [64, 70–75]. Consequently, another part of the association between anxiety disorders and CAD could be explained by the negative influence of these disorders on health behaviors and adherence to evidence-based risk-reducing recommendations and treatments for CAD [20, 21, 56, 64, 70, 75].

### Summary

Despite the recommendations of the American Heart Association in 2014 [18], very few studies have prospectively investigated the independent role and differential impacts of anxiety disorders on cardiovascular outcomes in patients with established CAD [33, 76]. While some studies assessed the prevalence and prognostic implications of GAD in patients with CAD, to our knowledge, no prospective study has documented the potential consequences of PD on these same outcomes.

Anxiety disorders, and more specifically PD and GAD, are associated with a wide array of unhealthy behaviors, but the prevalence and persistence of such behaviors in patients with CAD remain unknown. Moreover, no study has investigated the role of PD and GAD on enrollment, participation and adherence to cardiac rehabilitation. Finally, only one study accounted for both medical and behavioral risk factors while assessing the effects of GAD on adverse cardiac outcomes in patients with CAD [31]. This low number of studies combined with concerns regarding diagnostic accuracy in most of them severely limit the interpretation of the data available on this issue, underscoring the importance of further research on the prognostic significance of PD and GAD in patients with CAD.

### Objectives

In order to help bridge the knowledge gaps related to PD and GAD in patients with CAD, this study has two main objectives:To establish the prevalence and incidence of PD and GAD in the 2 years following a CAD-related revascularization procedure.To prospectively assess the association between the presence of PD or GAD and:Adverse cardiac events;Adherence to treatments (cardiac rehabilitation, pharmacotherapy);CAD-related health behaviors;Quality of life and psychological distress.

## Methods

### Design

This is a prospective cohort study in which participants will be evaluated at 5 time points: baseline, 3 months, 6 months, 1 year and 2 years. The study was registered with clinicaltrials.gov (NCT04433832).

### Participants

All adults (≥ 18 years) who undergo a CAD revascularization procedure at the coronary/cardiac surgical care unit of the Quebec Heart and Lung Institute and are fluent in French will be eligible for study participation. These patients will be recruited either onsite or following their transfer to the Hôtel-Dieu de Lévis University-Affiliated Hospital. Patients will be excluded if they present a severe communication problem or suffer from a terminal illness, a diagnosed major cognitive deficit, or any other condition that could invalidate the interview (e.g. psychotic disorder), of if they are not legally competent.

### Measures and outcomes definitions

#### Presence of PD and GAD (objective 1)

PD and GAD will be assessed at each time point using the Anxiety and Related Disorders Interview Schedule for DSM-5 (ADIS-5) [77]. This standardized interview protocol is one of the recommended measures for diagnosing anxiety disorders, including PD and GAD, in the research context [33, 78].

#### Adverse cardiac events (objective 2a)

Patients will be asked about all potential adverse events occurring during the study period with a structured medical interview developed by our team [79, 80]. All data will be confirmed by an independent review of medical records. With written consent from patients or next of kin (if deceased), records for admissions or consultations outside of the study hospital will be obtained from the hospital archives. Medical data will be extracted using a combination of a standardized medical data extraction form known for its excellent reliability (Cohen’s k = 0.72–0.91) and modules from the GRACE initial form [79–81].

Adverse events are defined as: either an acute myocardial infarction as defined by the Joint ESC/ACCF/AHA/WHF Task Force for the Universal Definition of Myocardial Infarction [82], a revascularization procedure (percutaneous coronary intervention or coronary bypass grafting), a cardiac arrest (including ventricular fibrillation) or death from a cardiovascular cause (primary cause).

The main outcome for objective 2a is the presence of any of the listed adverse events. The association between the presence of PD or GAD and each individual type of event will also be explored.

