#### Justification of sample size

The minimal sample sized required for each objective was calculated separately. The final sample size was established according to the objective requiring the highest number of participants (i.e. objective 2a, n = 2527 participants). That estimation was based on a previously reported rate of adverse cardiac events of 14.3% [22]. Considering an anticipated attrition rate of 30% after 2 years, a total of 3610 patients will have to be initially recruited. Based on the lower range of findings from studies of GAD in patients with CAD, the relative risk of adverse events in patients was conservatively estimated at 1.50 [33]. This data was used in the absence of similar studies in patients with PD.

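### The main outcome for objective 2a does not exclude revascularizations already planned at the index admission, so any that occur count as adverse events and pull the association toward no effect

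*Protocol article*

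**What the plan says.** All references are to the protocol article.

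- **Entry.** The Participants section makes eligible "All adults (≥ 18 years) who undergo a CAD revascularization procedure at the coronary/cardiac surgical care unit", subject to a language requirement and exclusions unrelated to revascularization. The abstract repeats that "3610 participants will be recruited following a CAD-related revascularization procedure".
- **Outcome.** Under Adverse cardiac events (objective 2a), the listed events are acute myocardial infarction, revascularization, cardiac arrest and cardiovascular death. Infarction is tied to a published universal definition, and death is limited to a cardiovascular primary cause. Revascularization is given only as "a revascularization procedure (percutaneous coronary intervention or coronary bypass grafting".
- **Composite.** "The main outcome for objective 2a is the presence of any of the listed adverse events". Each event type is also to be explored separately.
- **Window.** "Patients will be asked about all potential adverse events occurring during the study period". Assessments are at "baseline and follow-ups after 3, 6, 12 and 24 months". No rule is given for procedures scheduled before follow-up begins.
- **Sample size.** Objective 2a sets the size of the study. The inputs are "a previously reported rate of adverse cardiac events of 14.3" percent, a relative risk of 1.50, 2527 evaluable patients and 30% attrition.

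**The concern.** The same kind of procedure is both the entry criterion and a component of the outcome. In such a cohort, a revascularization during follow-up can mean two things: the disease has progressed or the first procedure has failed, or a treatment plan made at the index admission is being completed. Only the first is an adverse event in the sense of objective 2a. The second is decided before PD/GAD is assessed at baseline and cannot be a consequence of it. The stated definition does not separate them.

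Events of the second kind that occur equally often with and without PD/GAD add the same amount to both groups. The ratio moves toward 1, the difference shrinks slightly and the variance rises. This affects the objective that determined the sample size. Confirmation from medical records by staff blinded to the interview diagnoses establishes that a procedure took place. As the outcome is worded, it does not change whether the procedure counts.

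**Working it through.** **1. The plan's own figure.** 2527 / (1 − 0.30) = 3610, which agrees with the stated recruitment target. The 2527 itself cannot be uniquely reproduced, because the article does not give alpha, power or the exposed share. Some plausible settings come close: with two-sided 0.05 and 14.3% as the overall rate, 80% power with 10% exposed gives 2497, and 90% power with 15% exposed gives 2501.

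**2. Inputs for the dilution check.**

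- From Justification of sample size: 14.3%, RR 1.50, N = 2527.
- Assumed: 14.3% is the risk of genuine events in the unexposed, so the exposed risk is 0.143 × 1.50 = 0.2145.
- Assumed: a share s of patients has a planned second procedure, independent of PD/GAD and of other events; s = 2%, 5%, 10%. The article gives no figure.
- Exposed share: 10% (assumed) and 24% (the Background figure for GAD in patients with CAD). The article does not say which share was used.
- Assumed: two-sided 0.05, two-proportion test with pooled variance under the null.

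**3. Observed risks.** q = 1 − (1 − p)(1 − s).

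- s = 2%: unexposed 1 − 0.857 × 0.98 = 0.1601; exposed 1 − 0.7855 × 0.98 = 0.2302; ratio 1.44.
- s = 5%: 0.1859 and 0.2538; ratio 1.37.
- s = 10%: 0.2287 and 0.2931; ratio 1.28.

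The risk difference is multiplied by (1 − s), so it falls only from 7.15 to 7.01, 6.79 and 6.44 percentage points. Most of the power loss comes from the higher variance.

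**4. Power.** Power = Φ[(q1 − q0 − 1.96 × SE0) / SE1], where SE0 is the pooled and SE1 the unpooled standard error. For s = 0 with 10% exposed: (0.0715 − 1.96 × 0.02369) / 0.02684 = 0.93, giving 82%.

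| Planned share s | RR observed | Power, 10% exposed | Power, 24% exposed |
|---|---|---|---|
| 0% | 1.50 | 82% | 98% |
| 2% | 1.44 | 78% | 97% |
| 5% | 1.37 | 72% | 94% |
| 10% | 1.28 | 62% | 89% |

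**5. Other readings of the 14.3%.**

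- If it is the overall rate, the start is 80% power with 10% exposed, falling to 76% (s = 2%) and 69% (s = 5%), with RR about 1.43 and 1.36.
- If 4 of the 14.3 points are themselves planned procedures and only the other 10.3 carry the RR of 1.50, the exposed risk is 0.103 × 1.50 + 0.04 = 0.1945. The ratio is 0.1945 / 0.143 = 1.36. Power is 58% with 10% exposed and 85% with 24% exposed.
- If the 1.50 was estimated on a composite that already counted any revascularization, it already contains the dilution and there is no loss against plan.

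**The case against.** The strongest reply is that this rests on a missing phrase in a condensed article. Planned or staged procedures are never mentioned, and the extraction form and registry modules that the article cites are not shown and may record planned status. That stands as a limit on what can be claimed: a reader might infer that the investigators chose to count planned procedures, and the article does not say so. It does not remove the point. The article states a definition, with qualifiers on infarction and death and none on revascularization. A recorded planned status has no effect unless the outcome definition uses it.

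Three stronger readings are tempting and are not supported.

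- *The planned RR of 1.50 is diluted.* The article does not say which composite produced the 14.3% or the 1.50, so dilution relative to plan is conditional. The low power figures also need an assumed planned share together with a low exposed share.
- *A planned procedure hides later genuine events.* That would follow for a single any-event indicator or a first-event analysis. The Statistical analyses section describes generalized estimating equations with group by time terms over repeated assessments, under which a planned procedure before month 3 need not mask an infarction reported later.
- *Care seeking inflates the revascularization component in the exposed.* The Background says that both disorders involve "multiple and often unproductive medical consultations" and that their symptoms overlap with those of CAD. It does not say that these consultations lead to more procedures. The mechanism is plausible but not shown, and the planned exploration of each event type already addresses it in part.

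**Conclusion.** The point holds as a conditional one. Followed as worded, the definition counts procedures scheduled at the index admission as adverse events, in a cohort where everyone has just been revascularized. If such procedures occur and are unrelated to PD/GAD, the effect is misclassification, bias toward no association and lower power.

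The size cannot be fixed from the article. Over planned shares of 2% to 10%, an RR of 1.50 becomes 1.44 to 1.28. The loss of power runs from about 1 point (2% planned, 24% exposed) to about 20 points (10% planned, 10% exposed), and is nil against plan if the source RR already included all revascularizations. The definition should be corrected before analysis. The point does not show that the study is underpowered.

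**What to change.** - Define the component as a percutaneous or surgical revascularization during the study period that is not documented in the index-admission record as planned or staged.
- Add a field for planned status to the existing medical-record extraction form, completed by the same staff who are blinded to the interview results. Patients already enrolled can be coded from their index records.
- Report the composite with all revascularizations as a sensitivity analysis, which also keeps comparability with sources that used the wider definition.
- Optionally, pre-specify a supportive composite of infarction, cardiac arrest and cardiovascular death. This is a secondary addition, since the individual event types are already to be explored.

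The cost is one form field, one clause in the definition and some retrospective coding. The downside is a somewhat smaller event count. If the events removed are unrelated to PD/GAD, they carried no information on the association, so under the assumptions above power rises toward the 0% row of the table.

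### The main outcome of objective 2a counts any later PCI or bypass without excluding stages already planned at the index procedure, so scheduled completion of index treatment can score as an adverse event

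*Protocol article*

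**What the plan says.** The Participants section of the protocol article admits adults "who undergo a CAD revascularization procedure at the coronary/cardiac surgical care unit". The exclusions concern communication, terminal illness, cognition, conditions that would invalidate the interview, and legal competence. A further procedure still pending is not among them.

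The section on adverse cardiac events (objective 2a) gives a closed list: myocardial infarction by a named universal definition, "a revascularization procedure (percutaneous coronary intervention or coronary bypass grafting"), cardiac arrest, and death with a cardiovascular primary cause. It then states: "The main outcome for objective 2a is the presence of any of the listed adverse events". The window is the whole of follow-up: "Patients will be asked about all potential adverse events occurring during the study period", with assessments up to 2 years. Records are reviewed to confirm events, and under Procedures that review is blind to the diagnostic interview (ADIS-5). No section limits the revascularization component to unplanned procedures, sets an early period in which procedures do not count, or says that the record review separates scheduled from unscheduled ones.

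Objective 2a also fixes the sample size. Justification of sample size gives "objective 2a, n = 2527 participants", an event rate of 14.3%, and says that "the relative risk of adverse events in patients was conservatively estimated at 1.50".

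**The concern.** Some patients leave an index revascularization with a second stage already scheduled. If it takes place after enrolment, the definition makes that patient a case, although the procedure completes the index treatment and does not show that the disease has progressed. Objective 2 asks whether PD or GAD goes with a worse cardiac course, and a procedure decided at the index admission is weak evidence on that question.

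Two things are at stake. If planned stages are unrelated or only weakly related to PD/GAD, they act as false-positive events: the event rate rises and the relative risk is diluted in the objective that sets the size of the study. If they are strongly related to PD/GAD, for example because waiting for another procedure raises anxiety at the baseline interview, they could produce part of an apparent association. Planned stages would probably also fall early, so they would bear on the group-by-time models.

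**Working it through.** **The plan's own figure.** 2527 / (1 − 0.30) = 3610, which agrees with the stated recruitment target. The 2527 itself can be neither confirmed nor refuted, because alpha, power and the exposed share (PD or GAD) are not stated. With a two-sided 0.05 test of two proportions, it fits an exposed share of about 9–11% at 80% power, or 13–16% at 90%.

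**Inputs from the document.** N = 2527, event rate 14.3%, relative risk 1.50. The text does not say whether 14.3% is the overall rate or the rate in the unexposed. I take it as the unexposed rate p0, so p1 = 1.50 × 0.143 = 0.2145. Using it as the overall rate changes the results very little.

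**Inputs assumed.** The share s of patients with a planned stage after enrolment (1% to 10%); two-sided alpha 0.05; an exposed share f of 9.2% (gives 80% power at s = 0), 13.3% (gives 90%), or 24% (the lower of the two prevalences in the Background).

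**Case 1: planned stages independent of PD/GAD and added to the 14.3%.** The observed risks are

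q0 = p0 + s(1 − p0) and q1 = p1 + s(1 − p1).

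At s = 5%: q0 = 0.143 + 0.05 × 0.857 = 0.1859; q1 = 0.2145 + 0.05 × 0.7855 = 0.2538; the ratio is 1.37. Of the events in the unexposed, 0.0429 / 0.1859 = 23% would be planned procedures only.

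Power = Φ[(q1 − q0 − 1.96 × SE0) / SE1], with SE0 pooled and SE1 unpooled. At f = 9.2% and s = 0: (0.0715 − 1.96 × 0.0245) / 0.0279 ≈ 0.84, power 80%. At s = 5%: (0.0679 − 1.96 × 0.0271) / 0.0296 ≈ 0.50, power 69%.

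| s | q0 | q1 | RR | Power, f = 9.2% | Power, f = 13.3% | Power, f = 24% |
|---|---|---|---|---|---|---|
| 0 | 14.3% | 21.45% | 1.50 | 80% | 90% | 98% |
| 1% | 15.2% | 22.2% | 1.47 | 78% | 88% | 97% |
| 2% | 16.0% | 23.0% | 1.44 | 76% | 87% | 97% |
| 5% | 18.6% | 25.4% | 1.37 | 69% | 81% | 94% |
| 10% | 22.9% | 29.3% | 1.28 | 59% | 72% | 89% |

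To restore 80% power at f = 9.2%, the evaluable N would rise from 2527 to about 2680, 2840, 3330 and 4230 for s = 1%, 2%, 5% and 10%.

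**Case 2: planned stages already inside the 14.3%, with 1.50 applying only to the other events.** At s = 5% the unexposed risk stays 0.143 and the exposed risk is 0.05 + 1.5 × 0.093 = 0.1895. The RR is 1.33 and power at f = 9.2% is 48%. At s = 2% the figures are 1.43 and 69%.

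**Case 3: the cited 14.3% and 1.50 both describe an outcome that includes planned stages.** Then 1.50 is already the diluted ratio, and nothing is lost against the planned power.

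**Case 4: staging related to PD/GAD.** Let the planned share be s in the unexposed and k × s in the exposed, so q1 = p1 + k × s(1 − p1). At s = 5%:

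| k | RR of the composite |
|---|---|
| 1 | 1.37 |
| 1.2 | 1.41 |
| 1.5 | 1.47 |
| 2 | 1.58 |

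The composite ratio equals 1.50 when k = 1.5 × (1 − p0) / (1 − p1) = 1.5 × 0.857 / 0.7855 = 1.64. Below that the association is diluted, above it inflated.

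All power figures are for a crude comparison of two proportions at 2 years. The planned analysis is an adjusted generalized estimating equation model with a group-by-time interaction, so they show scale only.

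**The case against.** The strongest reply is that the article never says scheduled stages are counted. It calls the events adverse, has them confirmed from records, and uses a standardized extraction form that is not shown; coding of planned procedures might sit there. This does not remove the point. The article fixes a closed definition and qualifies its other components, such as the named definition of infarction and the cardiovascular primary cause of death. Only revascularization, the procedure by which every patient enters, stands unqualified.

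The objections on size do stand. The document gives no share of planned stages, and only stages after enrolment matter, so the number may be small. The exposed shares of 9.2% and 13.3% are solved to give 80% and 90% power; at 24% the fall at s = 5% is only from 98% to 94%. The cited rate and relative risk come from earlier studies whose outcome definitions are not shown, so the planned power may be unaffected.

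A reader might infer that the relative risk must move toward 1, because a stage decided before the baseline interview cannot follow from PD/GAD and so falls equally on both groups. The document does not support that. It describes both disorders as chronic, so they may predate the index procedure, and a pending procedure may itself raise baseline anxiety.

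There are partial safeguards: each event type is also explored separately, and record review is blind to the interview. The first lets infarction, arrest and death be read without revascularization, but the revascularization component stays mixed and the main composite is unchanged.

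**Conclusion.** The point holds as a defect of the stated outcome definition. Followed as written, it scores scheduled completion of index treatment after enrolment as an adverse event in the main outcome of the objective that sets the sample size.

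Dilution is the expected direction if staging is unrelated or only weakly related to PD/GAD. For planned shares of 2%, 5% and 10%, the relative risk falls from 1.50 to 1.44, 1.37 and 1.28, and 80% power falls to about 76%, 69% and 59%. These are illustrations that rest on an assumed share, alpha, power and exposed share. They do not show that the study is underpowered, which a reader might infer from them. At a share of 1% the effect is slight. With staging about 1.64 times as common or more in the exposed, the association is no longer diluted and can be inflated. In either direction the component measures something other than prognosis. The change is worth making because it is cheap and does not depend on which direction applies.

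**What to change.** In the definition of adverse cardiac events for objective 2a, count a revascularization only if it was not already planned at or before the index procedure or index admission. Add one field to the medical data extraction form (planned stage of index treatment: yes/no), completed by the reviewers already blinded to the ADIS-5. Report planned stages separately by group, and show the all-revascularization composite as a sensitivity analysis.

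The cost is one clause, one form field, slightly fewer events in the main outcome, and a judgment from the file on whether a procedure had been planned. For patients already enrolled, planned status could still be read from their files.
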